### Participant timeline {13}

Participant schedule for enrollment, interventions, assessments, and trial relevant visits can be visualized in Table 1.

**Table 1 Tab1:** SPIRIT flowchart of enrollments and assessments. Detailed timing for relevant events for participants during the randomized trial

	Study period						
	Enrollment	Allocation	Post-allocation				Close-out
Time point	$$\varvec{-t}_{\varvec{1}}$$	$$\varvec{0}$$	$$\varvec{t}_{\varvec{1}}$$	$$\varvec{t}_{\varvec{2}}$$	$$\varvec{t}_{\varvec{3}}$$	$$\varvec{t}_{\varvec{4}}$$	$$\varvec{t}_{\varvec{5}}$$
**Enrollment:**							
**Eligibility screen**	✕						
**Informed consent**	✕						
**Allocation**		✕					
**Interventions:**							
***FSH dose selection by model***			✕				
***FSH dose selection by clinician***			✕				
**Assessments:**							
***Baseline variables***	✕	✕					
***Outcome variables***				✕	✕	✕	✕

A detailed description of the timepoints reflected in the figure is as follows:$$-t_1$$: First appointment with the clinician where information on IVF/ICSI treatment is relayed to the patient. Information on the trial is communicated to the patient, and informed consent documentation is handed over to eligible patients. If any of the baseline variables needed for IDoser to function (age, BMI, AFC, and AMH) are not available at this time, steps are put in place to obtain relevant information for the next appointment. These can include petition of blood tests for AMH level results, or echography for AFC assessment.$$t_0$$: Appointment with the clinician where the signed informed consent form is retrieved. Patient is included if all baseline variables are available. Once included, the participant is allocated to either the IDoser FSH selection group or control group. The FSH dose is prescribed to the participant.$$t_1$$: First day of the COS protocol. Participant will self-administer the prescribed dose of FSH.$$t_2$$: Last ultrasound appointment prior to OPU. First outcome variables are registered (OHSS risk and OPU cancelation).$$t_3$$: Day of OPU. Further outcome variables are registered (number of COCs recovered, number of MII recovered and cancelation after OPU).$$t_4$$: Appointment to evaluate the presence of a fetal heart beat at the 7th week of gestation to establish whether pregnancy is achieved after first embryo transfer in current IVF/ICSI cycle. Presence or absence of clinical pregnancy is registered.$$t_5$$: End of study, considered after outcome on live birth after first embryo transfer is obtained. Presence or absence of live birth achieved is registered.Baseline variables include all necessary variables required for IDoser, including age of the patient, BMI, AFC, and AMH levels.

### Sample size {14}

A sample size calculation was performed to establish the number of participants required for the study. To determine a statistically significant difference equal or greater to 2 MII oocytes, 118 subjects are necessary in each group (*n *= 236), accepting an alpha risk of 0.05 and a beta risk of 0.2 in a one-sided test. We estimate a mean common standard deviation of 5.84 (as per the observational data included during development and validation of IDoser) and anticipate a drop-out rate of 10%.

### Recruitment {15}

All potential participants will be informed about the study by their clinician prior to undergoing IVF/ICSI treatment.

## Assignment of interventions: allocation

### Sequence generation {16a}

Stratified block randomization will be carried out depending on whether the patient is expected to be a poor responder (AMH < 1.2 ng/ml and AFC < 5, as per POSEIDON criteria [15]), high responder (AMH $$\ge$$ 3 ng/ml and AFC $$\ge$$ 15), or expected normo responder (any other case). This will ensure equal distribution of these patient etiologies across both arms. There will be 3 blocks (one for each strata) for every arm. The size of every block has been determined by the population distribution of each mentioned strata during the development and validation of the IDoser to be studied (13$$\%$$ poor, 15$$\%$$ high and 72$$\%$$ normo-responders) [11]. These figures translate to 15 patients in the poor responders group, 18 in the high responders, and 85 in the normo-responders within each arm. The study group (treatment or control) will be randomly assigned using a computer program with a 1:1 allocation ratio.

The 3 randomization lists will be generated using the online software Graphpad (http://www.graphpad.com/quickcalcs/randMenu/). This is a single-blinded trial, in which the patients are blinded to the source of the dose prescribed. Other clinicians apart from the one assigned to the participant, embryologists and part of the research team will also be blinded.

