## Methods: participants, interventions, and outcomes

### Study setting {9}

This is a randomized, single-blinded, multicenter, clinical trial. It will be carried out in two distinct centers in Spain, both of which are part of the same IVF group.

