## Interventions

### Explanation for the choice of comparators {6b}

Patients in the control group will be prescribed their first dose of FSH by the clinician in accordance with standard clinical practice.

Both participating centers adhere to a uniform clinical practice protocol, ensuring consistency in patient treatment and data collection across the trial. In both participating centers, eligible patients will undergo controlled ovarian stimulation, which can be induced with either recombinant FSH (Gonal®, Merck-Serono, Spain; Bemfola®, Gedeon Richter Iberica, Spain) or highly purified human menopausal gonadotropin or hMG (Menopur®, Ferring, Spain; Meriofert®; IBSA; Spain). The first dose of FSH, administered on the second day of the menstrual cycle, is routinely determined by expert physicians for specific patients depending on their age, ovarian reserve markers (AMH levels, AFC), and BMI. Pituitary inhibition will be performed with a GnRH antagonist (Orgalutran®, Organon, Netherlands), and ovulation will be triggered when $$\ge$$ 3 follicles of $$\ge$$ 17 mm diameter are observed, using 250 mcg of choriogonadotropin alfa (Ovitrelle®; Merck-Serono, Spain) or 0.3 mg of Triptorelin (Decapeptyl®, Ipsen Pharma, France) in cases with a risk of OHSS. Following oocyte retrieval, the sperm sample will be prepared for conventional IVF and/or ICSI. Fertilized oocytes will be cultured in vitro and transferred either fresh or frozen. The preferred clinical strategy is single embryo transfer on day 5 of embryonic development, although double embryo transfer and/or day 3 embryo transfer may be performed in specific cases.

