### Relevant concomitant care permitted or prohibited during the trial {11d}

Outside of first FSH dose allocation, the COS and IVF/ICSI treatments will be under control of the assigned clinician of the participant, as per routine practice.

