### Concealment mechanism {16b}

Single-blind trial. Participants will not be aware of which arm they have been placed in. Once the random allocation sequences are generated, they will be stored in an electronic data table accessible to the responsible clinician. Once the data for IDoser is introduced into the table, the arm allocation field will be populated with the next free sequence value of the participant strata. Apart from the data coordinator, the research team will also be blinded to participant allocation.

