#### Univariable analysis

Differences regarding the number of MII oocytes amongst the groups will be evaluated using Student’s *t* test or Mann-Whitney *U* test (if the distribution is not normal). These tests will also be used to compare FSH doses and COC number.

Regarding all categorical variables (OHSS risk, OPU cancelation, cycle cancelation, clinical pregnancy, live birth), differences between groups will be evaluated using Pearson’s chi-squared. Description of adverse events (if any) will be provided by the study group.

Alpha risk is set at a 5% for the primary analysis, focusing on the difference between MII oocytes retrieved between the two arms of the study. For secondary and subgroup analysis, appropriate statistical adjustment methods will be implemented.

All analyses will be performed using Python version 3.7.6. A *p*-value < 0.05 will be considered as statistically significant.

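### Centre is in neither the randomisation strata nor the stated primary test of this two-centre trial: a small, cheaply recovered loss of precision, not a bias

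*Protocol article*

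**What the plan says.** Study setting {9} describes two sites: "It will be carried out in two distinct centers in Spain, both of which are part of the same IVF group". Explanation for the choice of comparators {6b} adds that "Both participating centers adhere to a uniform clinical practice protocol, ensuring consistency in patient treatment and data collection across the trial".

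Sequence generation {16a} makes expected response the only stratification factor: "Stratified block randomization will be carried out depending on whether the patient is expected to be a poor responder", or a high responder, or a normo-responder. It then states that "The 3 randomization lists will be generated using the online software Graphpad". There is thus one list per responder class; separate lists for two centres would number six. Concealment mechanism {16b} confirms how a patient is allocated: "the arm allocation field will be populated with the next free sequence value of the participant strata". Centre plays no part in that draw.

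Under Univariable analysis, "Differences regarding the number of MII oocytes amongst the groups will be evaluated using" Student's t test or, if the distribution is not normal, the Mann-Whitney U test. Neither has a covariate. Outcomes {12} lists treatment centre among the demographic variables, so it will be in the dataset. The only use the article spells out for those variables is description by study group.

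**The concern.** The comparator is clinical judgement about the starting dose, and after that dose "the COS and IVF/ICSI treatments will be under control of the assigned clinician of the participant". Mean MII yield could therefore differ between sites. Nothing in the allocation scheme holds the two arms to the same centre mix, and the named test does not remove a difference in mix if one arises. Such a difference would move the estimated arm difference up or down relative to the 2-MII margin.

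At stake are a little power and the credibility of the one allocation that will be realised. If the arms visibly differ in centre mix and the centres differ in yield, a reader will ask whether the result reflects the dosing method or the site, and the unadjusted test gives no answer.

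**Working it through.** **Inputs from the article.** Margin 2 MII (Trial design {8}). SD 5.84, one-sided alpha 0.05, power 80%, drop-out 10%, 118 per arm (Sample size {14}). Responder classes of 15 poor, 18 high and 85 normo per arm (Sequence generation {16a}).

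**Assumptions, because the article gives neither figure.** Centre split p = 50:50. Difference in mean MII between centres D = 1 to 2.

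**1. The plan's own figure.** n = 2(1.645 + 0.842)² × 5.84² / 2² = 105.4, so 106 per arm. Then 106 / 0.90 = 117.8, so 118. The stated size is reproduced.

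**2. Standard error of the arm difference.** 5.84 × √(2/118) = 0.76 MII.

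**3. Chance difference in centre share between arms.** SD = √(p(1−p) × 2/n) = √(0.25 × 2/118) = 0.065, or 6.5 percentage points. The 95% range is ±1.96 × 6.5 = ±12.8 points. The chance of a gap above 10 points is 2(1 − Φ(0.10/0.065)), about 12%.

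**4. Shift in the primary difference.** Shift = gap in share × D. The 95% range is ±0.13 MII for D = 1 and ±0.26 MII for D = 2. With a 70:30 split it is ±0.12 and ±0.23.

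**5. Share of the sampling variance due to centre.** (D² × p(1−p) × 2/n) / (5.84² × 2/n) = 0.25D² / 34.1, which is 0.7% for D = 1 and 2.9% for D = 2. The n cancels.

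**6. Gain from adjusting.** Taking 5.84 as the total SD, the residual SD is √(34.1 − 0.25D²).

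| D (assumed) | Residual SD | n per arm needed before drop-out | Power at 106 per arm |
|---|---|---|---|
| 0 | 5.84 | 106 | 80.2% |
| 1 | 5.82 | 105 | 80.4% |
| 2 | 5.75 | 103 | 81.2% |

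**7. Type I error over all allocations.** Simulating the unadjusted t test at the margin (106 per arm, 40,000 runs) gave one-sided error rates of 0.049, 0.047 and 0.052 for D = 0, 2 and 3. There is no inflation.

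**8. Type I error given one unlucky allocation.** Suppose the centre gap is 10 points in favour of IDoser. With D = 2 the shift is 0.2 MII, or 0.2/0.76 = 0.26 SE. The chance of a false non-inferiority claim at the margin is then 1 − Φ(1.645 − 0.26), about 8%. With D = 1 it is 1 − Φ(1.645 − 0.13), about 6.5%. A gap in the other direction lowers the rate, which is why the average in step 7 stays at 5%.

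**9. Subgroups.** For 15 per arm the SD of the gap is √(0.25 × 2/15) = 18.3 points, so the 95% shift is ±0.36 (D = 1) to ±0.72 MII (D = 2). The standard error there is 5.84 × √(2/15) = 2.13 MII, using the overall SD because no subgroup SD is given. By step 5 the centre share of the variance is the same as in the whole trial.

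**The case against.** The strongest reply is that randomisation balances centre in expectation, and that what remains is ordinary sampling error already contained in the unadjusted standard error. This stands. A reader might infer that the trial is biased or that its error rate is inflated; step 7 shows that it is not. The figures of 8% and 6.5% apply only after conditioning on a particular imbalance.

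The article also points towards small centre differences: one IVF group and one clinical protocol. It nowhere says that each centre has its own clinicians; that is plausible but inferred. A common protocol limits centre differences without excluding them, because {6b} still leaves the control dose to physicians judging individual patients. This makes the assumed 1 to 2 MII uncertain and the true gain possibly smaller.

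A reader might also think the poor- and high-responder subgroups are the most exposed. In absolute MII they are. Relative to their standard errors they are not: they are imprecise because they hold 15 and 18 patients per arm.

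A further tempting claim is that results by centre would show whether the comparison depends on which clinicians are the comparator. With about 59 per arm in each centre, the standard error within a centre is 5.84 × √(2/59) = 1.1 MII, and that of the difference between centres is √2 × 1.1, about 1.5 MII. Such estimates could not settle the question.

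Finally, covariate adjustment may sit in an analysis plan that is not shown. That is possible, but the list structure and the primary test are stated choices here, and a later analysis plan cannot change how patients were allocated.

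**Conclusion.** The point holds as a minor one about precision and robustness. Centre is recorded, yet it appears in neither the randomisation lists nor the stated primary test. For a centre difference of 1 to 2 MII and an equal split, the chance shift is about ±0.13 to ±0.26 MII against a margin of 2, and adjustment is worth about 0.2 to 1 percentage point of power. Both the centre difference and the split are assumptions. Nothing here invalidates the planned conclusion or the sample size. The case for change is that it costs almost nothing and removes the dependence on how centres happen to fall between the arms.

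**What to change.** **Analysis (Univariable analysis).** Make the primary analysis a linear model of MII count on arm, with centre and responder class as fixed terms. Declare non-inferiority if the one-sided 95% lower confidence limit for IDoser minus control lies above −2 MII. Report arm differences by centre as description only.

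**Allocation (Sequence generation {16a}).** If recruitment has not started (Trial status says it had not at the time of writing), generate the lists by centre within responder class: 2 × 3 = 6 lists in small permuted blocks, so that no centre split has to be fixed in advance. If recruitment is under way, leave the lists alone and rely on the model.

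**Cost.** Centre uses one degree of freedom and responder class two. No extra data are needed and N stays at 236. A model replaces the bare two-sample test; the Mann-Whitney option cannot carry a centre term. With six lists the smallest cells may end on incomplete blocks, slightly loosening arm balance within responder class. Small blocks are also easier to guess for the treating clinician, who is not blinded, so block sizes should vary and stay undisclosed.

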### Concealment mechanism {16b}

Single-blind trial. Participants will not be aware of which arm they have been placed in. Once the random allocation sequences are generated, they will be stored in an electronic data table accessible to the responsible clinician. Once the data for IDoser is introduced into the table, the arm allocation field will be populated with the next free sequence value of the participant strata. Apart from the data coordinator, the research team will also be blinded to participant allocation.

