### Trial design {8}

The trial design is a single-blinded RCT with two arms with a 1:1 allocation ratio, comparing outcomes following FSH dose selection by IDoser and dosing based on standard clinical practice.

The hypothesis that will be tested is whether the performance of IDoser selecting the first dose of FSH is non-inferior to the standard clinical protocol in regards to the average number of mature oocytes recovered per group. The difference in the number of MII that is regarded to be clinically significant is 2 MII. Our decision to consider a difference of two MII oocytes as clinically significant is based on empirical evidence and clinical relevance. As only 30 to 40% of inseminated mature oocytes develop into blastocysts [13, 14], the choice of two MIIs strikes a balance between statistical significance and clinical practicality, while taking into account the consequent impact on the success of fertility treatments. If the average number of MII in the intervention group is inferior in 2 or more units, IDoser will be considered inferior to the standard clinical practice.

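### The control-arm first dose is chosen after the arm is revealed, by an unblinded clinician, and no intended clinician dose is committed before allocation

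*Protocol article*

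**What the plan says.** The t0 entry under Participant timeline {13} in the protocol article gives the order of events: "Once included, the participant is allocated to either the IDoser FSH selection group or control group. The FSH dose is prescribed to the participant". Table 1 places the two dose-selection rows at t1 and allocation at time 0, so it gives the same order.

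Concealment mechanism {16b} says what releases the arm: "Once the data for IDoser is introduced into the table, the arm allocation field will be populated with the next free sequence value". The table holding the sequence can be opened by the responsible clinician. Sequence generation {16a} and Who will be blinded {17a} both exempt the treating clinician from blinding.

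On the comparator, Explanation for the choice of comparators {6b} says: "Patients in the control group will be prescribed their first dose of FSH by the clinician in accordance with standard clinical practice". The same section states that both centers follow one practice protocol, and that physicians set the first dose patient by patient from age, ovarian reserve markers and BMI.

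Implementation {16c} describes one prescription per woman, from the clinician or from IDoser. The univariable analysis section plans a comparison of FSH doses between arms. No section describes a clinician dose committed before the arm is shown.

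**The concern.** In this trial the control treatment is a human judgement. If that judgement is made with the arm on the screen, it is made by someone who knows that this dose will be set against the model's. More caution, more ambition or more deliberation than usual would each move the control mean, and the trial would then compare IDoser with something other than standard practice.

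The second issue is interpretation. IDoser and the clinician use the same four predictors (age, BMI, AFC, AMH), and under {11d} only the first dose is set by the trial. A woman who would get the same first dose either way contributes no contrast between the methods. A finding of non-inferiority could then mean that IDoser's different choices do no harm, or that it rarely chose differently. Telling these apart with the protection of randomisation requires both doses for women in both arms. The planned between-arm dose comparison cannot show agreement within a woman.

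**Working it through.** **Inputs.** Margin, Trial design {8}: "The difference in the number of MII that is regarded to be clinically significant is 2 MII". SD, Sample size {14}: "We estimate a mean common standard deviation of 5.84". Error rates, same section: "accepting an alpha risk of 0.05 and a beta risk of 0.2 in a one-sided test". Drop-out 10% ({14}) and 1:1 allocation ({8}). The documents give no agreement rate between the methods and no size for a comparator shift. Both are assumptions below, shown as ranges.

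**1. The plan's own figure.** n per arm = 2 × (1.645 + 0.842)² × 5.84² / 2² = 105.4, rounded up to 106. Then 106 / 0.9 = 117.8, rounded up to 118. The stated 118 per arm is reproduced, with an assumed true difference of zero.

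**2. Standard error.** With 106 evaluable per arm, SE = 5.84 × √(2/106) = 0.802. If IDoser's true average loss is L, the probability of showing non-inferiority is P = Φ((2 − L)/0.802 − 1.645). At L = 0 this is 80%.

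**3. Agreement.** Let a be the share of women for whom the methods give the same dose, and D the loss in MII where they differ. Then L = (1 − a) × D.

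| a | D | L | P |
|---|---|---|---|
| 0% | 2 | 2.0 | 5% |
| 30% | 2 | 1.4 | 18.5% |
| 50% | 2 | 1.0 | 34.5% |
| 70% | 2 | 0.6 | 54% |
| 50% | 4 | 2.0 | 5% |
| 75% | 4 | 1.0 | 34.5% |

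Where L reaches 2, P is the nominal 5%. The rows with larger P have a true average loss inside the margin.

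**4. Comparator shift.** Suppose IDoser is truly 2.5 MII worse than undisturbed practice and the control arm moves a fraction s of the way toward IDoser, so that L = (1 − s) × 2.5. P is 1%, 7%, 24% and 53% for s = 0, 25%, 50% and 75%. In the other direction, suppose the policies are truly equal and knowing the arm raises the control mean by 0.5 or 1.0 MII. P then falls from 80% to 59% or 34.5%. These runs show sensitivity only; the documents support no particular s.

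**5. Precision where doses differ.** With 106 × (1 − a) women per arm and the same SD, the 90% CI half-width is 1.645 × 5.84 × √(2/(106 × (1 − a))).

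| a | Women per arm | Half-width (MII) | P if true difference is zero |
|---|---|---|---|
| 30% | 74.2 | 1.6 | 67% |
| 50% | 53.0 | 1.9 | 55% |
| 70% | 31.8 | 2.4 | 39% |

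**The case against.** The strongest reply is that the hypothesis concerns the group average (Objectives {7}, Trial design {8}), so the trial compares two dosing policies over all patients. If the methods mostly agree, IDoser really is non-inferior as a policy. A reader might take the 18.5%, 34.5% and 54% in step 3 as false-positive rates. They are not: the true average loss in those rows is 1.4, 1.0 and 0.6 MII, all inside the margin. This part of the reply stands in full.

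A reader might also infer that only one dose per woman is kept, and that nobody could ever say how often the methods differ. The documents do not support that. {16c} describes what is prescribed, not what is stored, and the article is condensed: its variable list names no dose although a dose comparison is planned. IDoser's inputs are held for every woman, so its dose for control women can be computed later if the model version is fixed, and agreement estimated from the control arm. That estimate would still rest on doses chosen with the arm known.

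The shift has no known direction, and the uniform practice protocol limits it. That also stands, but the protocol leaves the dose to the physician's judgement for each patient, so it does not remove the problem. Committing a dose first does not remove awareness of being in a trial; it removes knowledge of the arm. Finally, the differing-dose analysis is imprecise, and at 70% agreement its half-width exceeds the margin. It can be supportive only.

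**Conclusion.** The point holds as a weakness in the order of data capture. Allocation precedes dose choice, the chooser is unblinded, and no prior commitment is described. The control mean may therefore not represent standard practice; the direction and size of any departure cannot be known from the document. The clinician's intended dose for IDoser-arm women is lost once the arm is shown, and with it the only randomised comparison confined to women whose doses differ. No later analysis plan can restore it.

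Agreement costs interpretation, not validity. At 50% agreement the average would have to hide a 4 MII loss in the differing half before the 2 MII margin was reached. That figure assumes no difference where doses agree. The precision figures assume 106 evaluable women per arm and an SD of 5.84 in the subset. The stated sample size is reproduced and is not in question.

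**What to change.** Make the clinician's intended first dose a required, time-stamped field that must be completed before the arm field is populated. Carry it forward as the clinician's control-arm dose, and log any later change by the clinician with a reason. Store IDoser's output for every woman from a fixed model version, hidden from the clinician in the control arm.

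Report dose agreement. Repeat the randomised comparison in women whose two recorded doses differ, as a supportive, lower-precision analysis, with the definition of differing doses set in advance. Leave the primary analysis and the sample size as they are.

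The cost is one more field in an electronic table that already holds back the arm until data are entered, plus one extra analysis. Trial status says recruitment had not started at this version. There are two downsides: a small entry burden, and possible overrides when a clinician sees an IDoser dose unlike the one just entered. Under {11b} and {20c}, not receiving the allocated dose counts as withdrawal, so overrides should be logged and reported by arm.
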